##### Data analysis

The primary outcome measures comprise the levels of quality of life, well-being and the patients’ activation. The sociodemographic characteristics, health status, use of healthcare services and characteristics of the intervention are considered the secondary outcome measures. A statistical analysis will be conducted to analyse the association between primary and secondary outcomes. Furthermore, comparative measures between the baseline and follow-up 1, 2 and 3 will be computed, using generalized estimating equations (GEE) [29]. All analyses will be conducted using the IBM SPSS Statistics software, in the most recent version available.

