**Figure 2 F2:**
[figure not shown]
Moments of assessment.

The sample will include all the patients referred for the first time to a SP appointment who fulfil the inclusion criteria: being ≥18 years old and living in Lisbon. Patients who are terminally ill, who present severe and uncontrolled mental health issues (e.g. uncontrolled schizophrenia, acute psychosis), who are housebound, and who present uncontrolled use of drugs and/or alcohol are excluded from participation in the study. A recruitment target is estimated at 300 patients, with the chances of non-acceptance of participation and losses to follow-up (attrition rate) being estimated at >20%, based on previous studies [15,19,20,28].

All patients referred to SP in the first 12 months will be included in the baseline and the data collection will be conducted during 24 months. Both the patients who undertake SP activities and those who end their participation during data collection period will be included in the follow-ups.

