Moreover, this evaluation study also covers the experience of collaboration and perceived added value of intersectoral networks composed of different key actors. These topics have not been broadly addressed in published studies, and this exchange of information between the different levels of service provision – social and health sectors – can be valuable for the success of the SP intervention [33,36,37,38].

An expected limitation of this study is the challenges in generalizing the obtained results, since this is an evaluation of an SP intervention implemented in a local and specific context. The lack of a control group is a limitation of the Study 1 and therefore the results of this study will need to be interpreted with caution. It will be beneficial to conduct controlled studies in the future. Another limitation, previously described by other authors, is the possible loss of participants in the follow-up assessments [19,20], mainly in the last one (12 months) [28,39]. This possibility can arise from difficulties in contacting patients or non-attendance to scheduled appointments. Nevertheless, the findings of this study can contribute to assist the planning and implementation of SP and its evaluation in other contexts and countries.

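### Study 1 fixes GEE for the change from baseline although loss may depend on outcome, so the estimated change may be biased in either direction; a method valid under missing at random would be safer

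*Protocol article*

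**What the plan says.** Protocol article, Study 1, Data analysis: "The primary outcome measures comprise the levels of quality of life, well-being and the patients’ activation". The same paragraph says that "comparative measures between the baseline and follow-up 1, 2 and 3 will be computed, using generalized estimating equations (GEE", run in SPSS. It states no working correlation, weighting or imputation.

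Study 1, Design and participants: "A recruitment target is estimated at 300 patients", with "the chances of non-acceptance of participation and losses to follow-up (attrition rate) being estimated at >20" per cent. Assessments are at baseline and months 3, 6 and 12. Patients who stop taking part in activities are still meant to be followed.

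Study 1, Data collection: the follow-up questionnaire is given at the health unit ahead of social prescribing appointments.

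Discussion: the limitations include "possible loss of participants in the follow-up assessments [19,20], mainly in the last one (12 months"). On its causes: "This possibility can arise from difficulties in contacting patients or non-attendance to scheduled appointments". The lack of a control group is listed as well, with a call for cautious interpretation.

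**The concern.** GEE without weighting or imputation is guaranteed consistent only when missingness is unrelated to the outcomes, given the covariates in the model. Three features of Study 1 make that condition doubtful.

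- Outcomes are captured at appointments, so a patient who stops attending tends to have no score.
- Both causes of loss that the Discussion names, failed contact and missed appointments, could be linked to well-being or activation.
- The section SP in Portugal puts the intervention at around 4–6 appointments. Patients who finish or leave early may have no appointment at month 12, and the article names no other place for the questionnaire.

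In a single-group study the result is the change itself, and no comparison arm shares the selection. Any difference between patients who stay and those who leave goes straight into the estimate. Month 12 is the most exposed visit, and the Discussion presents the long follow-up as a strength of the design.

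**Working it through.** **The plan's own figure.** The target of 300 cannot be reproduced, because the article gives no alpha, power, effect size or SD. The point does not depend on it. The article also does not say whether 300 is before or after losses. If it is before, and if the whole 20% were loss to follow-up, 300 × 0.80 = 240 would remain. If it is after, 300 / 0.80 = 375 would have to be approached. Refusal precedes baseline and is not missing follow-up data, so the loss rate itself is not known.

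**What GEE estimates.** With a free mean at each visit and an independence working correlation:

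estimated change at month 12 = mean of those seen at month 12 − mean of all at baseline

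If the true change is zero, this equals the amount by which the remaining patients differ from the whole group. With a non-independence structure, earlier scores of lost patients enter the month-12 mean through the working correlation. The estimate is then corrected as far as that correlation is right.

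**Simulation A.** All inputs are assumptions except the four visits: 200,000 patients, true change 0, SD 1, equal correlation 0.5 or 0.7, and monotone dropout reaching 20%, 30% or 40% by month 12. Three mechanisms were used:

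- MCAR: loss is unrelated to scores.
- MAR: the log-odds of staying rise by 1.0 per SD of the previous score.
- MNAR: the same slope on the current, unseen score.

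Spurious change at month 12 in SD units (correlation 0.5 / 0.7):

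| Lost | Mechanism | Independence | Exchangeable | Unstructured |
|---|---|---|---|---|
| 20% | MAR | 0.098 / 0.134 | 0.006 / 0.004 | 0.007 / 0.007 |
| 30% | MAR | 0.152 / 0.203 | 0.012 / 0.008 | 0.014 / 0.010 |
| 40% | MAR | 0.199 / 0.272 | 0.010 / 0.009 | 0.009 / 0.008 |
| 20% | MNAR | 0.132 / 0.154 | 0.074 / 0.051 | 0.074 / 0.053 |
| 30% | MNAR | 0.197 / 0.232 | 0.110 / 0.080 | 0.112 / 0.084 |
| 40% | MNAR | 0.268 / 0.316 | 0.152 / 0.109 | 0.154 / 0.113 |

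Under MCAR no estimate exceeded 0.005 in absolute value.

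**Simulation B.** Same MAR slope, 15–45% lost, with the true correlation either equal across visits or weakening as visits lie further apart. Over these settings:

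- GEE with independence: about 0.07 to 0.27 SD.
- GEE with exchangeable: about 0.00 to 0.01 SD when that structure is true, and about −0.02 to −0.07 SD when the correlation decays.
- Likelihood with unstructured covariance: about 0.

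Visits at 0, 3, 6 and 12 months make a decaying correlation plausible. An exchangeable choice is therefore not a sure remedy.

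**Scale.** The SE of a paired change with 240 completers is √(2(1 − ρ)/240). That is √(1.0/240) = 0.065 SD for ρ = 0.5 and √(0.6/240) = 0.050 SD for ρ = 0.7. At 20% MAR loss, the independence bias is 0.098/0.065 ≈ 1.5 and 0.134/0.050 ≈ 2.7 of these SEs.

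**Direction.** All runs let low scorers leave, which produces a false gain under independence. Reversing the slope reverses every sign and leaves the sizes unchanged, because the assumed distribution is symmetric.

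**The case against.** The strongest reply is that the article names only GEE. Working correlation, weighting, imputation and sensitivity analyses are commonly left to a fuller plan, which is not shown. With a working correlation that fits, GEE is nearly unbiased under MAR. The large figures need an independence structure that the article never chooses. This stands: their absence is not the point, and no bias is shown. What remains is that the one method the article does fix is sensitive to the kind of loss the article itself foresees.

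A second reply is that the mixed model looks good because dropout was made to depend on observed scores, the condition under which it works. This also stands. Under MNAR, 0.05–0.15 SD remained with the exchangeable and unstructured structures. A mixed model weights the same data in the same way for a given covariance, so bias of that order should be expected there too.

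Third, the study is an exploratory pilot. It means to follow patients who stop, and it lists loss and the missing control group as limitations. That lowers the stakes but does not change how the estimate behaves. The Conclusions section still describes the work as robust and meant to inform policy.

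Several stronger readings are tempting, and the article does not support them:

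- **That more than 20% will be lost to follow-up.** The figure is "the chances of non-acceptance of participation and losses to follow-up (attrition rate) being estimated at >20" per cent, so refusal is included.
- **That loss is driven by non-attendance.** The Discussion gives it as one of two possible causes and says nothing about dependence on outcome.
- **That selective loss will look like improvement.** Patients who finish their plan because they improved could equally be the ones missed.

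**Conclusion.** The point holds as a conditional one. GEE is fixed for the comparison over time, its guarantee requires loss unrelated to outcome, and collection at appointments makes that assumption doubtful. The change may be biased upwards or downwards. A reader might infer that GEE needs MCAR and that the estimate therefore is biased. That does not follow: it depends on the mechanism, the working correlation and any weighting or imputation.

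Under assumed MAR dropout of 15–45% with a slope of 1.0 per SD, the size ranges from negligible (0.00–0.01 SD, correct exchangeable structure) through 0.02–0.07 SD (wrong structure) to 0.07–0.27 SD (independence). It is about zero for a likelihood analysis. The loss rates, slope and correlations are assumptions, and the article supplies none of them. The change of method is worth making because it is cheap and needs a weaker assumption, but it does not protect against MNAR.

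**What to change.** In Study 1, Data analysis, specify for the three primary scores a linear mixed model for repeated measures: all four visits as responses, time as a categorical factor, unstructured covariance, REML and all available data (SPSS MIXED). GEE after multiple imputation that uses prior scores and adherence is an acceptable alternative. Adherence is reported on forms by the community partners, so it can be known for patients who miss the questionnaire.

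Add one delta-adjusted sensitivity analysis that shifts the scores of lost patients over a stated range. It should go both up and down, since the direction of selection is unknown.

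In Design and participants, give expected refusal and expected loss to follow-up as separate figures.

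The cost is a few sentences of text, with the same data and software. The small downside is reliance on approximate normality, which matters most for the EQ-5D index and can be checked by bootstrap.

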#### Study 2 – Exploring experiences and suggestions of patients regarding SP

##### Design and participants

With the purpose of exploring experiences of patients during their participation on SP activities, a qualitative study will be conducted through semi-structured interviews to patients included in study 1.

Participants will be recruited during the follow-up 1 or in SP appointments. In cases where the patients completed the intervention plan or had given up the intervention or follow-up, they will be recruited with the cooperation of the social worker in contacting and inviting them for the study. Selecting patients with different socioeconomic characteristics (such as sex, age, employment status and migration background) and level of attendance to the intervention will help to obtain a diverse sample and distinct perspectives on this intervention.

Both the patients that are still in SP and those who had concluded their participation (i.e. who completed the SP intervention plan or who gave up the intervention) will be included. Those with significant hearing impairments, or with insufficient Portuguese/English speaking skills (when unaccompanied by a translator) will be excluded from participation.

##### Data collection

The participants will be contacted via phone call or email and invited to participate in a face-to-face interview. Interviews will take place in primary healthcare facilities or other location according to participants’ preference and availability.

A semi-structured guide will be used to conduct the interview with patients and will include questions about characteristics of the SP intervention, experiences on the SP activities performed, perceived changes in lifestyle, perspectives about positive and negative aspects of SP, opinions on the interactions with healthcare professionals and community partners, patient’s satisfaction with the SP intervention and suggestions for improvement. All interviews will be audio recorded.

Participants will be recruited until no new themes emerge from the data collected (data saturation) [30]. We estimate to interview 10 to 15 patients in each of the Primary Healthcare Units involved in the study.

##### Data analysis

Audio records of the interviews will be transcribed verbatim. Participants will revise the transcripts of their interviews for validation, to ensure its accuracy. Then, the transcripts will be anonymized for storage and scientific publication purposes. The transcripts of the interviews will be analysed through content analysis technique, as described by Bardin [31].

#### Study 3 – Understanding the perspectives of health professionals, social workers and community partners on the implementation of SP

##### Design and participants

Aiming to further understand the implementation of SP a qualitative study will be conducted through focus groups with health professionals (namely GPs, nurses and psychologists), social workers, and community partners involved in SP. The focus group technique, through group interaction, allows to broaden the understanding of the subject under study, its complexity and dynamic character, providing rich, valuable information and collective perspectives, and has been increasingly used in SP evaluation studies [32].

##### Data collection

In order to get the perspective of the stakeholders who have a role in the PS process, and based on the number of professionals involved in the SP intervention in Lisbon, five focus groups will be conducted: two focus groups with health professionals (namely GPs, nurses and psychologists), one focus group with social workers, and two focus groups with community partners. Each focus group will include 6–8 participants, resulting in an approximate total of 30 participants. Focus groups will be conducted by a moderator and a co-moderator of the research team.

A semi-structured guide will be used, covering common topics for all groups regarding perspectives on the process of implementing SP, barriers and facilitators, suggestions for improvement and experiences of collaboration and networking. In addition, each group will discuss about topics specifically related to their role in the SP intervention. The focus group sessions will be audio recorded.

##### Data analysis

Audio records of the focus groups will be transcribed verbatim. Participants will revise the transcripts of their focus group discussion for validation, to ensure the accuracy of the transcription. The transcripts will be anonymized for storage and scientific publication purposes. Content analysis will be performed to analyse the data, as described by Bardin [31].

#### Study 4 – Exploring the perceptions of the key actors about their networking experience

##### Participants, data collection and analysis

This study aims to explore the perceptions of the key actors involved in SP about their interactions and experience of collaboration within the intervention. This study draws on data collected in study 2 (interviews with patients) and study 3 (focus groups with health professionals, social workers, and community partners).

This study will focus on the collaboration between key actors, namely the interactions and exchange of information, the development of new responses, the challenges, lessons learned and perceived added value of acting in an intersectoral network.

The procedures for data treatment and analysis of the interviews and the focus group discussions are described in Study 2 and 3, respectively.

### Ethical considerations

Ethical approval for this evaluation study was obtained from the Ethics Committee of the Regional Health Administration of Lisbon and Tagus Valley (nº 5 2020/CES/2020).

In all studies, potential participants will be informed about the study’s objectives, data collection procedures, benefits and potential risks of participation. Participants will be assured that their participation in the study is voluntary and anonymous, and that the collected data is confidential. Participants will also be assured that refusing to participate or withdrawing consent at any moment will not entail any consequences, nor interfere with their participation in SP activities. After each participant agrees to participate, he/she will be asked to read and sign the informed consent. In study 1, this will take place prior to the first SP appointment, and in the studies 2 and 3 before the interviews and focus groups, respectively.

In study 1, the unique alphanumeric code will ensure that participation in the study is anonymous, and only the healthcare units’ professional will have the information needed to link the codes with patients’ personal information (name and contacts). The secondary data will be extracted, anonymized, processed and stored by the healthcare units’ professional, and then made available to the research team.

In studies 2, 3 and 4, an authorization to audio records the interviews and focus groups will be requested to each participant. The interviews and focus groups will be conducted in a private room to ensure the comfort of the participants and avoid interruptions.

Electronic data (data bases, computer files) will be stored as protected files with exclusive access of the research team. Paper-based data (questionnaires and consent forms) will be stored in locked cabinets in secure offices, only accessible by the research team. The identifiable information, such as participants’ names, will not be included in the transcriptions.

## Discussion

This evaluation protocol covers the three major dimensions where SP has potential impact: the patients, the collaboration between the health and social sectors, and the health system. This will be accomplished through triangulation of methods and information sources (quantitative measures along with in-depth interviews and focus groups) based on all key actors’ perspectives. Using such a broad evaluation scope will enable to obtain a diverse data corpus, allowing to explore in more depth the complexity of SP and its effects [33]. In fact, due to the interactions that occur between the various components of SP, as well as the number of groups or organisational levels involved, and the variability of outcomes, evaluating this kind of interventions implies to consider the context, the characteristics, the implementation process, the mechanisms of impact and the outcomes of the intervention [34].

In the patient’s dimension, the use of standardized, validated and repeated measures throughout time will provide a quantitative overview of SP’s contribution to individuals’ quality of life, well-being and activation. The WEMWBS, EQ-5D and PAM13 scales are the most frequent measuring tools used in SP evaluation studies [11,20]. Hence, the application of these scales, validated for the Portuguese context, increases the comparability with other studies. Furthermore, the number of assessment moments and long follow-up duration address weaknesses previously pointed out by several authors [11,20,33], since single and short (up to 4 months post intervention) follow-ups have been more commonly applied. A long follow-up interval has been considered essential to consistently measure the benefits of SP for both patients and the health system [17,35].

Moreover, the qualitative study will enable us to obtain in-depth insights on the patients’ experiences of participation in SP activities. Previous research on impact evaluation show that a qualitative approach can reveal strong positive narratives about the impact of SP in patients’ lives (such as improvements in feelings of well-being), even if the quantitative outcomes do not reflect these improvements (such as improvements in feelings of loneliness and social isolation) [19,20].

The SP’s impact on the collaboration between the health and social sectors will also be evaluated. Specifically, SP interventions and social responses provided to patients, and accepted and performed by them will be assessed using information from the quantitative, longitudinal study. The focus groups will provide information on articulation and communication between both sectors. Additionally, it will provide an insight into the health professionals’, social workers’ and community partners’ perspectives, which has only been obtained in few studies and remains an important gap in the literature regarding SP evaluation [19,20].

More broadly, the collection of information about the use of healthcare services will enable an evaluation of the influence of SP at the health system level. The relevance of assessing SP’s effects on this dimension has been previously highlighted [21,24]. SP responds to social needs that often lead patients to seek solutions in healthcare services. Thus, by providing effective responses to these needs, SP can contribute to reduce the overuse of healthcare services and the health professionals’ workload.

Besides the SP’s impact, this evaluation study also intends to provide useful knowledge on its process of implementation. The follow-up of all patients referred to SP, including those who conclude or withdraw their participation from SP activities before the follow-up evaluations represents an important innovation of this study. This will shed light on barriers to adherence to SP’s activities, while also allowing a comparison of outcomes between adherent and non-adherent patients.

Another differential of this evaluation study is that information on activities provided by community partners, accepted by patients and performed within SP will be collected and monitored for each participant. This will allow to collect detailed information about each patient’s pathway within SP, which has been described as a limitation in several studies [11,17]. It is acknowledged that the use of this approach is crucial to understand both the scope and the acceptability of the intervention among patients [34].

Moreover, this evaluation study also covers the experience of collaboration and perceived added value of intersectoral networks composed of different key actors. These topics have not been broadly addressed in published studies, and this exchange of information between the different levels of service provision – social and health sectors – can be valuable for the success of the SP intervention [33,36,37,38].

An expected limitation of this study is the challenges in generalizing the obtained results, since this is an evaluation of an SP intervention implemented in a local and specific context. The lack of a control group is a limitation of the Study 1 and therefore the results of this study will need to be interpreted with caution. It will be beneficial to conduct controlled studies in the future. Another limitation, previously described by other authors, is the possible loss of participants in the follow-up assessments [19,20], mainly in the last one (12 months) [28,39]. This possibility can arise from difficulties in contacting patients or non-attendance to scheduled appointments. Nevertheless, the findings of this study can contribute to assist the planning and implementation of SP and its evaluation in other contexts and countries.

